#### Data analyses

Statistical analyses will be performed with IBM SPSS statistics version 20.0 and the level of significance is set at p < 0.05. Primary and secondary outcome variables will be analysed according to intention-to-treat (ITT) and per protocol (PP). In ITT analyses, all participants allocated to the study groups constitute the study sample, whereas only participants that complete a minimum of 14 treatment sessions (≥50% of the total number of treatment sessions) and have valid measurements at baseline and follow-up will be the study sample in the PP analyses. In analyses of the main hypothesis, effect size and the treatment effect (between-group mean differences and 95% CI) will be determined for the primary and secondary outcome variables by means of analysis of covariance (ANCOVA) utilising mixed model approach, with treatment as fixed factor and baseline measurement of the outcome variable as covariate. If the residuals of an ANCOVA model are not normally distributed, appropriate transformations of relevant variables will be used in the analysis. Full model for post hoc tests will be used. For the variable General Improvement (PGICS) comparisons between the groups will be made by proportional odds model (ordinal logistic regression) and estimation of the absolute effect (risk difference) with 95% CI.

Analyses regarding the secondary aim to evaluate the importance of physical and psychosocial factors in the workplace on long-term treatment outcomes will be handled in the following way. Participants that show an improvement exceeding minimal clinically important difference for the primary outcomes (6 NDI% or 15 NRS%), at follow-up 1 (one week after intervention), will be classified as “improved”. Long term effects (measured at 12-month follow up) of workload factors on primary outcome variables and the secondary variable Capacity on the quality and quantity to work will be tested for the group “improved” with General Linear Model ANCOVA where outcome values at follow-up 1, as well as the factors for work load exposure (see *Questionnaires*), are covariates. Exposure of workload is measured 1 week after end of intervention. At 6-month and 12-month follow-up participants answer questions on if exposure has changed the latest 6 month. Those whose self-rated physical or psychosocial work exposure markedly changed (measured with 2 questions) between follow-up 1 and 12-month test will be excluded for further analyses related to the secondary aim.

The third aim to evaluate the cost-effectiveness in the groups, cost-utility analyses (CUA) comparing measures of health gain and measures of costs will be performed
[82]. For this purpose, estimates of quality adjusted life year (QALY) gains based on EQ-5D will be calculated, followed by cost by QALY ratio.

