**Methods/Design:**

120 working women with minimum six weeks of nonspecific neck-shoulder pain aged 20–65, are allocated by minimisation with the factors age, duration of pain, pain intensity and disability in to the groups tailored treatment (T), non-tailored treatment (NT) or treatment-as-usual (TAU). Treatment is given to the groups T and NT for 11 weeks (27 sessions evenly distributed). An extensive presentation of the tests and treatment decision model is provided. The main treatment components are manual therapy, cranio-cervical flexion exercise and strength training, EMG-biofeedback training, treatment for cervicogenic headache, neck motor control training. A decision algorithm based on the baseline assessment determines the treatment components given to each participant of T- and NT-groups. Primary outcome measures are physical functioning (Neck Disability Index) and average pain intensity last week (Numeric Rating Scale). Secondary outcomes are general improvement (Patient Global Impression of Change scale), symptoms (Profile Fitness Mapping neck questionnaire), capacity to work in the last 6 weeks (quality and quantity) and pressure pain threshold of m. trapezius. Primary and secondary outcomes will be reported for each group with effect size and its precision.

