## Methods/Design

### Design and setting

The study is a prospective interventional single-centre, single-assessor, blinded randomized controlled clinical trial. Participants with neck-shoulder pain will be allocated in a 1:1:1 ratio to either tailored (T) or non-tailored (NT) treatment two to three times a week for 11 weeks (in total 27 sessions) or to treatment-as-usual (TAU). Minimisation
[21,22] is used for the allocation sequence to minimise imbalance on the factors age, duration of pain, average pain intensity last week (Numeric Rating Scale – NRS) and disability due to neck pain (Neck Disability Index – NDI). Further, comparisons of baseline assessments will be performed with a control group without neck pain. The study will be executed in Umeå, Sweden. Assessment (questionnaires, laboratory and clinical assessments) of the participants with neck-shoulder pain is made one week before and after the treatment period, with follow-up measurements 6 and 12 month after end of treatment. The 12 month follow-up is only performed with questionnaires. See Figure
1 for a flow chart of the study. The study was approved by the Regional Ethical Review Board in Uppsala, Sweden (registration number 2011/081) and informed and written consent from participants is obtained according to the Declaration of Helsinki.

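### The effect models leave out most of the minimisation factors; the analysis stays valid, but is conservative and gives up some precision to the extent that those factors predict outcome

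*Protocol article*

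**What the plan says.** The abstract's Methods/Design paragraph states that participants "are allocated by minimisation with the factors age, duration of pain, pain intensity and disability". The Design and setting section repeats this: minimisation is used "to minimise imbalance on the factors age, duration of pain, average pain intensity last week" and, as fourth factor, disability on the NDI, with a 1:1:1 ratio. Two of the four factors are thus the baseline values of the two primary outcomes.

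The Data analyses section fixes the model for continuous primary and secondary outcomes as an ANCOVA by a mixed-model approach, "with treatment as fixed factor and baseline measurement of the outcome variable as covariate". For the change scale it says: "For the variable General Improvement (PGICS) comparisons between the groups will be made by proportional odds model", together with a risk difference and 95% CI. No covariate is named there.

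The only other wording on model content is "Full model for post hoc tests will be used". It is not defined and names none of the minimisation factors.

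**The concern.** Minimisation makes the arms more alike on the chosen factors than simple randomisation would. If a factor predicts outcome, the treatment contrast then varies less from one allocation to another. A model that omits the factor leaves its contribution in the residual and computes the standard error as though the factor had been left to chance. The reported standard error is then larger than the true one, so intervals are wider than they need be and the test rejects less often than its nominal 5%.

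At stake is how well the error rate and the reported precision match the allocation method, and part of the benefit for which the trial minimised. Freedom from bias and control of false positives are not at stake.

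**Working it through.** The plan gives no figure on this point, so there is none to reproduce. The prognostic strength of the factors is not in the documents; every percentage of variance below is an assumption.

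**Step 1. What each model omits.**

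| Outcome | In the model | Minimisation factors omitted |
|---|---|---|
| NDI | treatment, baseline NDI | age, duration, NRS |
| NRS | treatment, baseline NRS | age, duration, NDI |
| ProFitMap symptom index, work capacity, pressure pain threshold | treatment, own baseline | all four |
| PGICS | treatment | all four |

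**Step 2. Type I error by formula.** Let R² be the share of residual variance (after own baseline) due to the omitted factors. If all of it were perfectly balanced, the true error rate of a nominal 5% test would be 2 × (1 − Φ(1.96/√(1 − R²))):

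- R² = 5%: 1.96/√0.95 = 2.011, rate 4.4%
- R² = 10%: 1.96/√0.90 = 2.066, rate 3.9%
- R² = 15%: 1.96/√0.85 = 2.126, rate 3.4%

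This is the extreme case. The documents do not say how the factors are coded for minimisation. If they were split at the median, about 64% of a normal covariate's variance would be balanced. Replacing R² by 0.64 × R² gives about 4.6%, 4.3% and 3.9%.

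**Step 3. Simulation of the continuous outcomes.** Inputs from the protocol: 120 participants, three arms, four factors, and a difference of 6 NDI% with SD 10.3 (6/10.3 = 0.58 SD). Assumed: median splits, the best arm taken with probability 0.8 and otherwise a random arm, own baseline explaining 36% (last row 25%) of outcome variance, and the other three factors adding 0-15% of total variance. There were 1,500 runs per setting. Widths are in SD units from the no-effect runs. The closed-form width ratio is √((1 − own)/(1 − own − added)).

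| Own / added | CI width, planned | CI width, all four | Ratio, simulated | Ratio, closed form | Type I error, planned | Power, planned | Power, all four |
|---|---|---|---|---|---|---|---|
| 36% / 0% | 0.708 | 0.712 | 0.994 | 1.000 | 0.039 | 0.896 | 0.891 |
| 36% / 3% | 0.710 | 0.697 | 1.018 | 1.024 | 0.047 | 0.889 | 0.896 |
| 36% / 6% | 0.709 | 0.678 | 1.046 | 1.050 | 0.047 | 0.907 | 0.927 |
| 36% / 10% | 0.713 | 0.657 | 1.085 | 1.089 | 0.035 | 0.923 | 0.949 |
| 25% / 15% | 0.765 | 0.688 | 1.113 | 1.118 | 0.041 | 0.859 | 0.911 |

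The width ratios agree with the closed form once the small cost of extra covariates is allowed for. The type I rates are noisier: the Monte Carlo standard error is √(0.05 × 0.95/1500) = 0.006, and the first row, where the true rate is 5%, came out at 0.039. They support a rate at or below nominal, but do not rank the rows.

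Most of the extra width is an overstated standard error, not a noisier estimate. At 10% added, the actual spread of the planned estimate was 0.168 against 0.163 with all four factors, only 3% more (0.168/0.163 = 1.03), while its interval was 8.5% wider.

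**Step 4. PGICS.** Assumed: five categories, each factor with a log odds ratio of 0.45 per SD, a true treatment log odds ratio of 1.1 for power, and 400 runs.

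| | No covariate | Four factors |
|---|---|---|
| Model SE, no effect | 0.399 | 0.411 |
| Actual SE, no effect | 0.355 | 0.401 |
| Type I error | 0.030 | 0.043 |
| Mean log odds ratio, true effect 1.1 | 0.99 | 1.18 |
| Power | 0.685 | 0.785 |

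Adjustment does not shorten the log-odds interval; the model SE rises slightly. It brings model and actual SE together, and the conditional log odds ratio is larger, which is where the power comes from. With factors of no prognostic value, power was 0.78 without and 0.79 with adjustment. The Monte Carlo standard error of a 5% rate here is √(0.05 × 0.95/400) = 0.011, so the two type I figures are only indicative.

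**The case against.** The best defence is that this is a cheap efficiency gain on an analysis that is already valid. Each primary outcome's own baseline, probably its strongest predictor, is in its model. The own baselines of the other continuous outcomes may carry part of the same information. Nothing is lost if the factors add nothing. All of that stands, and it limits the size of the point. It does not remove the mismatch: the article states its covariate set, so this is not a detail left to an analysis plan that is not shown.

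Four stronger readings are tempting, and the documents do not support them.

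- *The omission inflates false positives.* The direction is the opposite: error is at or below 5%.
- *The precision is needed because NDI power is below 0.8.* Such a shortfall concerns the covariate-free ANOVA in the Power section and is a separate matter. In the simulated ANCOVA above, planned power for a pairwise difference of 6 NDI% was 0.859-0.923, given an assumed 25-36% of variance explained by the baseline.
- *All intervals are too wide by a known amount.* The size depends on a prognostic strength that is not documented, and for PGICS adjustment does not narrow the log-odds interval.
- *PGICS should have had its own baseline as covariate.* A change rating has no baseline value, so that absence is no inconsistency. The minimisation factors are simply the natural adjusters there.

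**Conclusion.** The point holds as one of efficiency and calibration. The stated models omit three or four of the minimisation factors, and the consequence is conservative.

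For NDI and NRS the loss is modest. Over an assumed 0-15% of added variance, the planned interval runs from 0.6% narrower to about 11% wider than with all four factors. Power changes from half a point in the plan's favour (0.896 against 0.891) to about 5 points against it (0.859 against 0.911). Type I error is about 3.5-4.7% by simulation. For PGICS the loss may be larger, about 10 power points (0.685 against 0.785), but only under the assumed strength of 0.45 per SD for each factor, and PGICS is a secondary outcome.

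The omission and its direction are certain. The size is not, because it rests on assumed prognostic strength, median-split coding and a random element of 0.8 in the minimisation.

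**What to change.** In the Data analyses section:

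1. Add age, duration of pain, baseline NRS and baseline NDI, as continuous covariates, to every ANCOVA/mixed model, alongside the outcome's own baseline.
2. Add the same four covariates to the proportional odds model for PGICS, and report its odds ratio as conditional on them.
3. Obtain the PGICS risk difference and its 95% CI by standardisation from that adjusted model.
4. Define what the full model for post hoc tests contains, so that it agrees with items 1 and 2.

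No new data are needed, since minimisation requires all four values before allocation. The cost is a few sentences and 3-4 degrees of freedom out of 116 (120 participants less four parameters in the planned model). If the factors add nothing, the interval widens by about 1%: 0.6% in the simulation, and √(116/113) − 1 = 1.3% by a rough formula that ignores the balance achieved by minimisation.

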## Abstract

**Background:**

A major problem with rehabilitation interventions for neck pain is that the condition may have multiple causes, thus a single treatment approach is seldom efficient. The present study protocol outlines a single blinded randomised controlled trial evaluating the effect of tailored treatment for neck-shoulder pain. The treatment is based on a decision model guided by standardized clinical assessment and functional tests with cut-off values. Our main hypothesis is that the tailored treatment has better short, intermediate and long-term effects than either non-tailored treatment or treatment-as-usual (TAU) on pain and function. We sub-sequentially hypothesize that tailored and non-tailored treatment both have better effect than TAU.

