### Statistical methods

#### Power

Power calculations with the one-way analysis of variance (ANOVA) routine (nQuery Advisor 3.0) are presented with regard to treatment effects for the primary outcome measures Physical functioning, and Average pain intensity last week. For physical functioning measured with NDI, a clinical important difference is between 6–10 NDI%
[81]. Reference data from a parallel clinical trial (ISRCTN92199001) showed that the NDI standard deviation (SD) was 10.3 NDI% (based on 117 women with neck-shoulder pain). To obtain a power of 0.8, given a difference of 6 NDI% between any of the three groups, 20 individuals are required in each group (alfa = 0.05). For the average pain intensity last week, the smallest clinical important pain reduction measured with NRS is approximately 15%
[43]. In the above mentioned clinical trial, the SD was 15.5 NRS%. Given these facts, 20 individuals in each group is sufficient to obtain a power of >0.8 for a difference of 15 NRS% between any of the three groups (alfa = 0.05). On the basis of this power calculation we aim at recruiting 40 participants for each group, which would give us a satisfactory safety margin to retain a power of 0.8 or higher through the trial.

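### The non-normality fallback can move the primary NDI and NRS estimates off the scale of the promised mean differences; the handling of the three follow-ups should also be stated

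*Protocol article*

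**What the plan says.** The main hypothesis, in the abstract's Background, is that "tailored treatment has better short, intermediate and long-term effects than either non-tailored treatment or treatment-as-usual (TAU) on pain and function". Under Design and setting, assessment "is made one week before and after the treatment period, with follow-up measurements 6 and 12 month after end of treatment", which gives three post-treatment time points.

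The Data analyses section states the planned result: "effect size and the treatment effect (between-group mean differences and 95% CI) will be determined for the primary and secondary outcome variables". The method is ANCOVA by a mixed model approach, "with treatment as fixed factor and baseline measurement of the outcome variable as covariate". No other model term is named.

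The next sentence is the fallback: "If the residuals of an ANCOVA model are not normally distributed, appropriate transformations of relevant variables will be used in the analysis". It does not say how non-normality is judged, which transformation is used, whether outcome, baseline or both are transformed, or how the result is brought back to the original scale.

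The benchmarks are on the original scale. The Power section says "For physical functioning measured with NDI, a clinical important difference is between 6–10 NDI" (in per cent) and sizes the trial for between-group differences of 6 NDI% and 15 NRS%. The secondary-aim analysis uses the same two figures as minimal clinically important differences.

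**The concern.** A mean difference in NDI% and a difference in, say, square-root NDI are different quantities. The plan promises the first and, under a condition checked on the trial's own data, switches to something like the second. Three consequences follow when the outcome is transformed.

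- The estimate and its CI can no longer be compared directly with 6 NDI% or 15 NRS%.
- The condition attaches to each ANCOVA model separately, so NDI and NRS, or the same outcome at different follow-ups, could be reported on different scales.
- Both the decision to transform and the choice of transformation come after the residuals are seen, with no rule limiting either.

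A second, smaller matter is that the hypothesis concerns three horizons, while the named terms are only treatment and baseline. The reader cannot tell whether a separate model is fitted at each follow-up or one model covers all three.

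**Working it through.** The plan gives no figure of its own to reproduce here. The check asks what a fixed effect on a transformed scale means in NDI%.

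**Inputs from the protocol.** Promised estimate: mean difference with 95% CI (Data analyses). Benchmarks: 6 NDI% and 15 NRS% (Power). NDI at entry: 10 to 68 (Table 1). NRS: 0 to 10 (Questionnaires). No pain last week on the NRS is a listed result (Other outcome measures, item 1).

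**Assumed, because the protocol names none.** The transformation (square root or log), the effect on that scale, and the comparator scores m. Scores after treatment can lie below the entry minimum of 10.

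**Square root.** With comparator score m and an effect δ on the root scale, the difference in NDI% is m − (√m − δ)² = 2δ√m − δ². For δ = 0.6:

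- m = 9: 9 − 2.4² = 9 − 5.76 = 3.24
- m = 25: 25 − 4.4² = 25 − 19.36 = 5.64
- m = 50: 50 − (7.071 − 0.6)² = 8.13

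The same estimate passes 6 NDI% where 1.2√m − 0.36 = 6, so √m = 5.3 and m = 28.09. Below that comparator score it is under the benchmark, and above it, over.

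In the other direction, a 6 NDI% difference on the root scale is √m − √(m − 6):

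- m = 12: 3.464 − 2.449 = 1.015
- m = 20: 0.730
- m = 30: 0.578
- m = 40: 0.494

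No single root-scale value corresponds to 6 NDI%.

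**Log.** The effect becomes a ratio r, and the difference is (1 − r)m. For r = 0.80 this is 2.4, 4, 6 or 8 NDI% at m = 12, 20, 30 or 40. Conversely, 6 NDI% is a ratio (m − 6)/m of 0.50, 0.70, 0.80 or 0.85 at those scores. Back-transformed log means are geometric means, so back-transforming does not restore the difference in arithmetic means. The log is undefined at NRS 0, a result the protocol expects, so an added constant would be one more unplanned choice.

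**Visits.** A simulation used 300 runs, 40 women per group, and assumed tailored-minus-usual-treatment effects of −8, −6 and −1 at the three follow-ups. Treatment and baseline were the only terms.

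- All visits stacked, no time term: one estimate of −4.99, close to the average (−8 − 6 − 1)/3 = −5.
- One fit per visit: −7.92, −6.03 and −1.03, close to each assumed effect.

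The named terms are therefore enough if fitted at each follow-up, but not if the visits are stacked.

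**The case against.** **On the transformation.** The clause is conditional: with acceptable residuals everything stays in NDI% and NRS%. It does not rule out reporting on the original scale as well, and if only the baseline covariate were transformed, the treatment effect would stay in original units. No specific transformation is named, so the square-root and log figures are illustrations. A reader might infer that 6 NDI% and 15 NRS% are decision rules for the group comparison and that the primary result would then go unanswered. The protocol does not say so: it uses the figures to size the trial and to classify individual women as improved, and that classification is unaffected by a model transformation. All of this stands. It limits the consequence but leaves a stated rule that, once applied to the outcome, replaces the promised quantity with one the plan does not define.

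**On the visits.** A reader might infer that the named model cannot produce short-, intermediate- and long-term effects at all. The protocol does not support that. Nothing in it says visits are stacked without time, the wording allows a separate ANCOVA per follow-up, and the full model mentioned for post hoc tests is undefined and could include time. Covariance and other repeated-measures detail may properly sit in a fuller plan.

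A reader might also infer that per-visit ANCOVA breaches the intention-to-treat definition by dropping women who miss a visit. That definition says who belongs to the sample, not how missing values are handled. The protocol gives no attrition figure, and a repeated-measures model would itself omit women with no follow-up. Neither inference is relied on here.

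**Conclusion.** The point holds for the transformation clause. If it is triggered and the outcome is transformed, the primary estimate ceases to be a mean difference in NDI% or NRS%, on a scale chosen after seeing the data. In the illustrations, one transformed effect corresponds to anything from 3.24 to 8.13 NDI% (square root, 0.6) or 2.4 to 8 NDI% (ratio 0.80), on either side of 6. Those sizes rest on the assumed transformations, effects and comparator scores. That the scale changes does not.

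The protective value of the clause is small. With about 40 women per group, non-normal residuals matter little for an adjusted mean difference, and robust or bootstrap intervals deal with what remains.

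On visits, the finding is only an ambiguity. The three contrasts are available from per-visit fits, and the text should say which approach is meant. Overall this is a change that should be made, not a flaw that invalidates the trial.

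**What to change.** 1. Replace the transformation sentence with a fixed rule: the primary analyses of NDI and NRS are done and reported on the original scale whatever the residuals look like, with robust or bootstrap 95% CIs. Any transformed analysis is labelled as sensitivity and does not replace the primary result.

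2. Add one sentence on visits. Either state that a separate ANCOVA is fitted at each of the three follow-ups or, preferably, specify one repeated-measures mixed model per outcome with visit and treatment-by-visit terms, reading the treatment contrasts at each visit. The single model also keeps women with partial follow-up in the analysis.

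The cost is two sentences of text and slightly more analysis work. The repeated-measures option adds a few parameters. Neither change affects recruitment, assessments or treatment.
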